# A service evaluation of the implementation of a novel digital intervention for hypertension self-monitoring and management system in primary care (SHIP): protocol for a mixed methods study

**DOI:** 10.1186/s12872-024-04279-y

**Published:** 2024-12-19

**Keywords:** Hypertension, Self-monitoring, Blood pressure, Telemonitoring, Digital intervention, Implementation

## Abstract

**Background:**

Hypertension is a key risk factor for death and disability, and blood pressure reduction is associated with significant reductions in cardiovascular risk. Large trials have shown that interventions including self-monitoring of blood pressure can reduce blood pressure but real-world data from wider implementation are lacking.

**Aim:**

The self-monitoring and management service evaluation in primary care (SHIP) study will evaluate a novel digital intervention for hypertension management and medication titration platform (“Hypertension-Plus”) that is currently undergoing initial implementation into primary care in several parts of the UK.

**Methods and analyses:**

The study will use a mixed methods approach including both quantitative analysis of anonymised electronic health record data and qualitative analyses of interview and customer support log data. Pseudonymised data will be extracted from electronic health records and outcomes compared between those using the digital intervention and their own historical data, as well as to those not registered to the system. The primary outcome will be difference in systolic blood pressure in the 12 months before and after implementation. A further analysis will utilise self-monitored blood pressure data from the Hypertension-Plus system itself. Semi-structured qualitative interviews will be completed with implementation and clinical leads, staff and patients in six general practices located in two different geographical areas in England. Informed by the non-adoption, abandonment, scale-up, spread, and sustainability (*NASSS*) framework, our analysis will identify the challenges to successful implementation and sustainability of the digital intervention in routine clinical practice and in patients’ homes.

**Ethics and dissemination:**

The analyses of pseudonymised data were assessed by the sponsor (The University of Oxford) as service evaluation not requiring individual consent and hence did not require ethical approval. Ethics approval for the qualitative analyses was provided by Wales REC 4 (21/WA/0280) and individual written informed consent will be gained for all participants. Results will be published in peer-reviewed journals, presented at national and international conferences and disseminated via patient and health service organisations.

**Discussion:**

This study will provide an in-depth analysis of the impact and acceptance of initial implementation of a novel digital intervention, enhancing our understanding and supporting more effective implementation of telemonitoring based hypertension management systems for blood pressure control in England.

## Background

Hypertension is a key risk factor globally for death and disability, and in the United Kingdom (UK) it is the most common long-term condition, currently recognised in over 8 million adults (14%) [1]. Improved blood pressure (BP) control is associated with significant reductions in cardiovascular risk: every 5mmHg systolic pressure reduction will reduce coronary heart disease (CHD) risk by approximately 10% and stroke risk by 20% [2].

However, such benefits are limited by factors such as health care system failure, clinical inertia in escalating BP lowering therapy and reduced patient adherence leading to sub-optimal use of proven interventions, notably antihypertensive medication [2, 3]. Key interventions which address these three issues, and have been shown to be cost-effective, include digital interventions facilitating patient self-monitoring and self-management [4, 5]. Both have been shown to support patient engagement and increased self-efficacy, to be effective at engaging clinicians, and to achieve improved BP control mainly through better management of medication. Little work has assessed the impact of such interventions on a wider scale. In Scotland, a simple text based telemonitoring system has been implemented and evaluated via the Scale-Up Programme [6]. To our knowledge, this will be the first evaluation in England of the “real-world” implementation into daily practice of a hypertension telemonitoring system, outside of the framework of a trial.

The self-monitoring and management service evaluation in primary care (SHIP) study aims to evaluate the challenges of implementing of a novel digital intervention in England and to assess its impact in terms of uptake, BP control and workload.

## Methods

### Study design and setting

The SHIP Study is a primary care based mixed methods study of the implementation of a digital self-monitoring/self-management intervention in general practices from three areas in England. The study comprises both quantitative and qualitative elements assessing real world implementation using routinely collected data alongside a qualitative process evaluation.

### Participants

Primary care practices implementing a novel digital intervention for hypertension management (the Hypertension-Plus service) will be invited to take part in this study by email approach initially followed by a remote site initiation meeting. The study will include pseudonymised data from people in participating practices including both users and non-users of Hypertension-Plus. To facilitate data extraction, practices need to be members of or prepared to join the Oxford Royal College of General Practitioners Clinical Informatics Digital Hub (ORCHID) [7].

### The intervention

The digital intervention (“Hypertension Plus”) was provided by Omron Healthcare combining blood pressure telemonitoring with prompts for hypertension management including medication titration intended to facilitate remote care [4]. The intervention is based on workflow algorithms developed from research data and decision support tools designed to be compliant with National Institute for Health and Care Excellence (NICE) guidelines [8].

The system combines a web-based dashboard for professionals, which both reads and writes data to the practice clinical system, with a mobile phone “app” which is downloaded by participating patients and used to upload BP readings. Patients are invited to use the digital intervention via contact from their practice and then sign up via a bespoke web interface. The choice of which patients receive an invitation is at the discretion of practices, but they are typically people with raised BP receiving antihypertensive treatment plus some without a diagnosis of hypertension. Telephone and online support is provided for those people having problems accessing or engaging with the technological platforms.

The digital intervention is a commercial system and is licenced annually, usually at local healthcare organisation level (known as primary care networks (PCN) or Integrated Care Boards in England). Implementation is being led by Omron working with the National Association for Primary Care (NAPC, https://napc.co.uk) and includes training for practices, support with identification of appropriate groups, support for patients, and peer led support facilitated by the NAPC.

### Quantitative study

Pseudonymised coded and numeric clinical data will be extracted using the Oxford-Royal College of General Practitioners Clinical Informatics Digital Hub (ORCHID) system [7]. ORCHID is a secure system that regularly extracts pseudonymised data from member practices for disease surveillance, quality improvement and research purposes (https://orchid.phc.ox.ac.uk/index.php/orchid-data/). Data will not be extracted from records of patients who have opted out of use of their health records in research. The analysis will take place within the ORCHID trusted research environment. Outside of ethically approved trials with individual consent, no individual data leaves this network. All aggregate data extracts subject to statistical disclosure control.

People invited to use the digital intervention will be compared to patients on the practice hypertension register who have not been invited. Outcomes will be assessed using predefined curated variables of Systematised Nomenclature of Medicine (SNOMED) clinical terms (CT) codes (Fig. 1; see https://github.com/[name] for codelists) [9].

(Fig. 1)

The most recent routinely collected retrospective data extracted at baseline will include:

Age (years).Sex.Ethnicity.Smoking status.Index of Multiple Deprivation (IMD), a measure of socioeconomic status.Height, weight, body mass index (kg/m2).Total and HDL cholesterol (mmol/L).Systolic and diastolic blood pressure (clinic and/or home readings).Pulse.Past medical history:Diagnosis of diabetes (Type 1 or 2).Previous myocardial infarction or stroke.Diagnosis of chronic kidney disease.Medication useStatin treatment (drug type and dose).Antihypertensive medication use.Other current cardiovascular medication.Electronic Frailty Index (eFI) and/or characteristics required to calculate this.Health Economic Resource use: relevant consultations, referrals and admissions as available.Practice identifier (pseudonymised).

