### Outcomes

### Primary outcome

The primary outcome will be change in systolic blood pressure (SBP, clinic and home BP both included) in mmHg extracted from the electronic healthcare record comparing 12 months before and after intervention implementation along with comparison between those on the hypertension register invited to use and not invited to use the intervention.

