### Statistical analysis

Descriptive statistics will be presented as the means and standard deviation (SD), proportions, and medians with interquartile ranges where appropriate. In the efficacy analyses for blood pressure, mixed-effects model repeated measures will be used to compare the changes in BP for people on the hypertension registers (i.e. with a clinical code for hypertension) between one year before and one year after implementation of the digital intervention within each practice. Fixed effects in the model are the exposure, whether BPs are measured (home or clinic), periods (12 months before and after implementation), interaction terms between the exposure and time period variable and covariates that were selected a priori because they have been reported to show correlations with both BP and cardiovascular (CVD) risk and could potentially confound the association between BP and CVD risk. These potential confounders will include baseline demographic characteristics (age, sex, ethnicity, IMD and frailty), clinical characteristics at baseline (SBP and DBP, total cholesterol, smoking, antihypertensive medication use), past history (diabetes, established cardiovascular disease, and chronic kidney disease). Random effects for patient and practice level average BP will also be included in the model. These covariates were selected a priori because they have been reported to show correlations with both BP and CVD risk and could potentially confound the association between BP and CVD risk [12]. Covariates are defined using the closest available electronic healthcare records data prior to baseline. The intervention analysis will take a similar approach albeit limited to the self-monitoring group and the variables included in the Hypertension-Plus dataset.

A 5% significance level will be used for all analyses/ tests.

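### Invited status has no date while the after year runs from practice implementation, so any invitation made during that year selects comparators partly on their outcome

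*Protocol article*

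**What the plan says.** Protocol article, Quantitative study: "People invited to use the digital intervention will be compared to patients on the practice hypertension register who have not been invited". Primary outcome repeats this as a "comparison between those on the hypertension register invited to use and not invited to use the intervention". Neither section gives a date or window at which status is read. The abstract words the contrast differently, comparing users with their own history "as well as to those not registered to the system".

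The time axis comes from another section. Statistical analysis compares BP "between one year before and one year after implementation of the digital intervention within each practice", so both years hang on the practice's start date and not on a patient's invitation. The effect is carried by "interaction terms between the exposure and time period variable", with baseline SBP and DBP among the covariates.

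On who is invited, The intervention says: "The choice of which patients receive an invitation is at the discretion of practices, but they are typically people with raised BP". It does not say whether invitations go out in one batch or continue over time.

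**The concern.** Take a register patient who is uninvited at go-live and has a high reading six months later. If the practice then invites that patient, he or she is no longer an uninvited comparator. A similar patient whose readings stay low remains one. Group membership then depends on the readings being compared, and the comparators' after-period mean drops with no change in care.

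Re-dating only the invited patients would not cure this, because the never-invited group would still be filtered on its own after-period readings. Nor does the planned baseline adjustment: a baseline value is constant within a patient, so with balanced readings it leaves the exposure-by-period coefficient unchanged.

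At stake is the size, and possibly the sign, of the primary between-group estimate.

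**Working it through.** The plan gives no figure for this bias. Its 91% power statement does not bear on it.

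**Inputs from Sample size:** mean SBP 148, patient SD 17, measurement SD 10, effect -3 mm Hg. Practice SD is left out of the main runs because both groups come from the same practices.

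**Assumptions, not in the plan:** 2 readings before and 4 after; true effect 0; an uninvited patient is invited with probability 0.10, 0.25 or 0.50 after each after-period reading at or above 140, 150 or 160. The 140 value is the plan's clinic control limit; no invitation threshold is stated. Each scenario has 400,000 simulated patients.

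**Estimate:** D = (after mean - before mean) in the invited, minus the same in the never-invited. With balanced readings this is the exposure-by-period coefficient of a random-intercept model. Positive D works against the intervention.

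1. *No go-live invitations, all rolling.* Never-invited change: -0.2 to -1.3 mm Hg (threshold 150: -0.2, -0.5, -1.1). D = +0.9 to +2.05.

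2. *20% invited at go-live regardless of BP, then rolling.* D = +0.5 to +1.7.

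3. *20% invited at go-live from those whose last before-period reading met the threshold, then rolling.* D, in mm Hg:

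| Invitation probability | 140 | 150 | 160 |
|---|---|---|---|
| 0.10 | -0.35 | -1.0 | -2.3 |
| 0.25 | +0.4 | +0.1 | -0.9 |
| 0.50 | +1.2 | +1.0 | +0.35 |

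Repeat runs put the lowest cell at -2.2. The comparators' own change is positive in four of the nine cells.

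4. *All invitations at go-live, on raised BP.* D = -1.7 to -3.9. A hand check at threshold 140, inviting a quarter of those who qualify:
   - SD of one reading = sqrt(17² + 10²) = 19.72; z = (140 - 148)/19.72 = -0.406; share qualifying = 0.657; density at z = 0.367; ratio = 0.559.
   - Expected error in the triggering reading = (10²/19.72) × 0.559 = 2.83. Averaged over two before readings, the invited change is -2.83/2 = -1.42.
   - Invited share = 0.25 × 0.657 = 0.164, so the comparator change is +1.42 × 0.164/0.836 = +0.28.
   - D = -1.42 - 0.28 = -1.70. Simulation gives -1.70 to -1.72.

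**Which side the bias comes from.** With 2 + 2 readings, threshold 140 and rolling probability 0.25, the invited change is +1.35 and the never-invited change is -0.58, so D = 1.35 + 0.58 = 1.93. Much of D is therefore invited patients' own high pre-invitation readings counted as after. When those readings are dropped (2 before, 4 after), +0.1 to +1.3 mm Hg remains, essentially all from the comparators.

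**Other reading patterns.** With 2 + 2 or 4 + 4 readings, mean 148 or 138, threshold 140 and all invitations rolling, the comparator shift is -0.2 to -1.3 and D is +0.8 to +3.2.

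**The case against.** The strongest reply is that rolling invitation is assumed. The article describes help for practices in identifying suitable groups, which fits a single list at roll-out. The flow chart of quantitative procedures is not visible in the text used here, and a condensed article may leave the date for reading exposure status to a fuller document. This stands in part: nothing in the text says that status is determined at the end of the after year, or that patients with high BP in fact leave the comparator group. A reader might infer both, but they follow only if invitations continue. What survives is that the article does state a comparator and a time origin, and the two are not tied together.

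A second reply also stands. A reader might conclude that this bias always hides benefit. It does so when go-live invitations ignore BP, but the article says invitees typically have raised BP, and regression to the mean then pulls the other way (items 3 and 4). For the same reason, invitation only at go-live removes this particular mechanism but does not make the comparison unbiased.

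Third, the largest comparator shift, 1.3 mm Hg, needs about 71 to 77% of the register to be invited. When go-live invitations based on raised BP were mixed with rolling ones at threshold 140 and balanced readings, the shift was only 0.04 to 0.4.

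Finally, re-indexing at invitation without further adjustment can do more harm than the fault, because the triggering reading falls in the before window. Spurious benefit was about -0.3 to -3.5 mm Hg in one set of runs and -1.7 to -4.5 in another that used only two pre-index readings including the trigger. This is why the fix below carries an adjustment.

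**Conclusion.** The point holds conditionally and should be acted on. If invitations continue into the after year, uninvited status depends on after-period SBP. The comparator shift is about -0.2 to -1.3 mm Hg when no BP-based invitation takes place at go-live. The net exposure-by-period bias is about +0.5 to +2 mm Hg when go-live invitations ignore BP or there are none, and about -2.2 to +1.2 when they follow raised BP. In absolute terms this reaches 2/3 = 67% to 2.2/3 = 73% of the assumed 3 mm Hg effect.

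The documents do not support a fixed direction, and opposing biases of unknown size do not make the estimate safe. The sizes rest on the assumed reading pattern, thresholds, invitation rates and go-live share, none of which the article gives.

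**What to change.** Tie group status and time origin to the same date:

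- At each invitation date (or month), take as comparators register patients in the same practice not yet invited on that date, and give them the same index date.
- Stop a comparator's readings at any later invitation; that patient may then enter the invited group from his or her own date.
- Match on, or adjust the post-index readings for, pre-index SBP readings including the most recent one, so that the triggering reading does not create regression to the mean. With this addition the bias was near zero in every scenario run.
- Keep individual readings in the model. Averaging each comparator's readings up to the stop would bring selection back, since stopping tends to follow a high reading.
- Report how many comparators were later invited, and keep the never-invited comparison as a sensitivity analysis.

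If all invitations were in fact sent at go-live, say so, fix status at that date and use the same adjustment. The abstract's comparator wording should be brought into line.

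Cost: more programming, using invitation dates; some comparator readings dropped; and patient-clustered standard errors, because a patient can appear in both groups. Adjustment removes regression to the mean only as far as invitation depends on the recorded readings.

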### Blood pressure data

Readings will be identified as having been taken by a healthcare professional in the clinic or by the patient at home. Where multiple readings are recorded on a single day, the lowest value will be selected. BP readings outside of the range systolic BP (SBP) < 70 or > 260 mm Hg or diastolic BP (DBP) < 40 or > 150 mm Hg will be discarded following standard editing rules [10].

### Data management

SNOMED CT code lists of the clinical features will be curated by clinical researchers, epidemiologists, and SQL developers to form the curated variables. The primary analysis will use Quality and Outcomes (QOF) business rules SNOMED clinical term definitions for the population and all relevant SNOMED codes to define co-morbidities [11]. QOF is a pay-for-performance chronic disease management system in the United Kingdom. Bespoke algorithms will be developed for data extraction, filtration, manipulation, and exploratory data analysis (EDA). Code lists are available (https://github.com/[name]).

### De-identified intervention data

In addition to the routine clinical data extracted via ORCHID from the electronic health record, anonymised ‘process’ measures (including how many registered, medication, co-morbidity and self-monitored BP data) will be separately extracted from the stand-alone Hypertension-Plus database. Further information regarding this is presented after the ORCHID analysis.

### Outcomes

### Primary outcome

The primary outcome will be change in systolic blood pressure (SBP, clinic and home BP both included) in mmHg extracted from the electronic healthcare record comparing 12 months before and after intervention implementation along with comparison between those on the hypertension register invited to use and not invited to use the intervention.

### Secondary outcomes

Diastolic blood pressure (DBP) in mm Hg, extracted from the electronic healthcare record or the Hypertension-Plus system in the same manner as SBP readings using the same comparison as the primary outcome. A sensitivity analysis considering SBP and DBP in the same way as the primary analysis will include those with uncontrolled BP prior to implementation of the intervention. Controlled BP will be defined as SBP < 140 mm Hg and DBP < 90 mm Hg for clinic readings or SBP < 135 mm Hg and DBP < 85 mm Hg for home readings. Uncontrolled BP will be defined as the presence of any clinic or home SBP or DBP reading at or above these thresholds.

Primary care hypertension workload defined as the number of consultations where hypertension or hypertension monitoring was listed as the primary problem will be compared before and after implementation in a similar way to the BP outcomes.

### Exploratory outcomes

Exploratory outcomes include the evaluation of the impact of the digital intervention on antihypertensive medication use and other cardiovascular preventative treatment (statins, antiplatelets, anticoagulants). Subgroups (see below) will be examined for the comparisons defined in the primary outcome.

Further exploratory outcomes will be addressed using the standalone intervention data. These are detailed below in the Hypertension-Plus outcomes and analysis section.

### Sample size

Sample size requirements for this study were determined through simulation. A mean BP of 148 mm Hg was assumed, with practice variation (standard deviation, SD) of 5 mm Hg. Within a practice, patient variation (SD) was assumed as 17 mm Hg and measurements within a patient were assumed to vary by 10 mm Hg (SD) about the patient mean. Effect size was assumed to be -3 mm Hg (BP 3 mm Hg lower in patients using the digital intervention) and a minimum of 4 BP measurements for each patient. This demonstrated that to achieve 90% power at the 5% significance level, 100 patients each drawn from 8 general practices would be required for this study (800 patients in total, 91% power). Assuming greater variation (practice SD = 10 mm Hg, patient SD = 22 mm Hg or measurement SD = 14 mm Hg), the required sample size was 100 patients from 14 practices respectively. The available sample will depend upon the implementation rate as well as recruitment and will include as many patient records as are available.

